## Abstract

**Background:**

Radiation therapy to upper abdominal sites is technically challenging due to motion of tumors and surrounding organs resulting from normal respiration. Breath-hold, using an Active Breathing Coordinator is one strategy used to reduce motion in these tumor sites. Though widely used, no studies have prospectively compared the different breath-hold techniques (inspiration, deep-inspiration and expiration) using ABC in the same patient cohort.

**Methods:**

Patients planned for radiation therapy to upper abdominal tumors are invited to participate in this prospective study. Participants attempt three breath hold techniques: inspiration, deep-inspiration and expiration breath-hold, in random order. kV fluoroscopy images of the dome of diaphragm are taken of five consecutive breath-holds in each technique. Reproducibility and stability of tumour position are measured, and used to select the technique with which to proceed to planning and treatment. Reproducibility at planning and each treatment fraction is measured, along with breath hold time, treatment efficiency and patient experience.

**Discussion:**

The screening method was validated after the first three participants. This screening process may be able to select the best breath-hold technique for an individual, which may lead to improved reproducibility. The screening process is being piloted as a prospective clinical trial.

***Trial registration*:**

Australian New Zealand Clinical Trials Registry (ANZCTR): 12618001691235. Registered 12th October 2018. https://www.anzctr.org.au/Trial/Registration/TrialReview.aspx?id=376109&isReview=true.

## Background

Radiation therapy (RT) to upper abdominal (UA) sites, including liver, pancreas, kidneys and adrenal glands, is technically challenging. This is due to the proximity of the tumor to organs at risk (OAR), and OAR motion due to both respiration and physiological variation, such as filling of gastro-intestinal organs [1].

Breath-hold (BH) techniques, either voluntary or assisted, have been implemented to minimize respiratory-induced motion [2–7]. Inspiration Breath-Hold (IBH), Deep-Inspiration Breath-Hold (DIBH) and Expiration Breath-Hold (EBH) are reported in the literature [3–7]. Employing a voluntary IBH technique has demonstrated cohort reproducibility (R_BH_) of 4–10 mm [3, 8, 9], whilst voluntary EBH has demonstrated cohort R_BH_ of 2–5 mm [3, 9]. When an Active Breathing Coordinator (ABC)™ device (Elekta, Stockholm, Sweden) is used to assist breath-hold, improvements in R_BH_ have been seen, with DIBH intra-fraction cohort R_BH_ of 1.3–1.6 mm [6, 7], and EBH intra-fraction cohort R_BH_ of 1.5 mm [10]. Although EBH techniques tend to display a better R_BH_ at a cohort level, in many studies the R_BH_ ranges for different BH techniques overlap [3, 9]. This suggests that patients may be able to perform multiple breath hold techniques adequately enough for IGRT. Although population level estimates for the average cohort R_BH_ and S_BH_ have been done, none yet aim to select the best method for each patient.

There is limited literature available to describe patients’ experience of BH. A recent study evaluated 150 patients’ experiences of voluntary BH using MR-guided RT using an un-validated questionnaire [11]. Considerable difficulty controlling their tumor position in voluntary BH was reported by 12.5% of patients [11]. Another study investigated the patient experience of DIBH, in 41 patients receiving breast RT [12]. More than 90% of participants rated their experience > 8 on a 10 point Likert-type scale (where 0 = not at all; 10 = extremely) for ease, comfort and control of BH using ABC [12]. To our knowledge, no studies have investigated patients’ experiences of multiple BH techniques.

## Methods

### Study design and ethics

The aims of this study are to evaluate the R_BH_ and stability (S_BH_) of tumor position; patient experience; and efficiency of treatment delivery for each BH technique. This is a prospective, single-institution study of adults, aged over 18, undergoing RT for malignancies of the liver, pancreas, adrenal gland and kidney. Patients suitable for RT, including Stereotactic Ablative Radiotherapy (SABR) techniques are eligible and invited to participate. The study was approved by our institutional Human Research Ethics Committee (HREC 47012). Once identified, eligible participants are provided with written information about the study from their Radiation Oncologist (RO) or the study coordinator. Informed consent is mandated prior to enrolment. Figure 1 provides an overview of study procedures.

**Fig. 1 Fig1:**
[figure not shown]
Study schema

### Primary outcome measures

aR_BH_ and S_BH_ of UA tumors in IBH, DIBH and EBH, measured pre-planning.bNumber of participants screened into each BH technique.cR_BH_ of UA tumors at planning, in participant’s selected technique.dInter-fraction and intra-fraction R_BH_ of UA tumors at each treatment fraction, in participant’s selected technique.

### Secondary outcome measures

aTreatment efficiency of IBH, DIBH and EBH, in participant’s selected technique.bPatient-reported experience of IBH, DIBH and EBH, measured pre-planning.

## Study procedure*s*

### Breath-Hold Assessment

All participants undergo protocolled education with ABC, then an assessment to confirm their ability to ABC-BH (Fig. 2a–c: ABC Device). Participants are screened for eligibility in IBH, DIBH and EBH in random order to reduce risk of bias, using a pre-determined block randomization sequence. Eligibility, breath-hold time (T_BH_) and ABC-BH threshold are recorded for each technique.

*T*_*BH*_ Time (seconds) that the participant can BH comfortably, at least three times.

*ABC-BH Threshold* Volume of air (liters) in the participant’s lungs at BH activation. The radiation therapists determine the threshold with the participant, as follows:

*EBH* 0.0–0.2 L*IBH* Peak volume of air during normal, relaxed respiration. Average of three measurements.*DIBH* Maximum peak volume of air during voluntary deep inspiration. Threshold is 80% of average of three measurements.

**Fig. 2 Fig2:**
[figure not shown]
Active Breathing Coordinator™ components. **a** Mouth-piece and spirometer; **b** nose-peg and control switch; **c** operators screen displaying activated EBH indicated by green bar

### Pre-planning reproducibility and stability

To assess R_BH_ of tumor position between consecutive BHs, and S_BH_ of tumor position during each BH, 5 kV X-ray fluoroscopy images are acquired in each BH technique on an Elekta™ linear accelerator, using the XVI™ software “MotionView” function. The position of the tumor, or an appropriate surrogate (diaphragm or fiducial marker), is tracked. Each image is acquired anterior–posteriorly (AP) (Fig. 3), for the complete duration of each of the participant’s BH’s. R_BH_ and S_BH_ are defined as follows:*R*_*BH*_ Cranio-caudal position of the tumor/surrogate at the beginning of BH1 is compared to the position at beginning of BH2-5. Four observations are recorded per technique. The absolute value (ignoring direction) of the cumulative sum of each observation is determined, and then averaged.*S*_*BH*_ Cranio-caudal displacement of the tumor/surrogate, during each BH. Five observations are recorded per technique. The mean of the absolute value (ignoring direction) of each observation is then calculated.

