### Determination of treatment technique

Following the ABC-BH and pre-planning R_BH_ and S_BH_ assessments, selection of treatment technique is made according to the decision matrix (Fig. 4), with R_BH_ prioritized. If two or more techniques have equal (to nearest mm) mean R_BH_, then the technique with better S_BH_ is selected. A technique with mean R_BH_ and/or S_BH_ > 5 mm will proceed to free-breathing.

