### Planning reproducibility

Participants have all subsequent planning and treatment using the chosen BH technique. Four planning computed tomography (CT) scans are acquired for each participant. The scans are acquired sequentially within a 5 min timeframe, with no patient-repositioning between scans, to minimize the impact of repositioning or physiological variation. The Gross Tumor Volume (GTV), tumor surrogates and OARs are contoured on the first planning CT. Post-processing and measurements are completed using a customized workflow in MIM Maestro® software (MIM Software Inc, Cleveland OH). The first planning CT is automatically fused to subsequent CTs. Initially, a bone algorithm fusion corrects any gross patient misalignment. Then, a tumor, surrogate or fiducial marker fusion corrects for tumor/organ position. Contours are automatically generated onto each subsequent CT. Resultant contours are reviewed, and manually edited if required to account for deformation. The inter-BH displacement of the tumor and OARs are measured, with bone fusion as the starting position. Planning R_BH_ of tumour/surrogate and OARs is defined as follows:*R*_*BH*_ Position, in three planes, of the tumor/surrogate or OAR contour centroid and contour surface in CT1 compared to the position in CT2-4, resulting in three observations. The mean of the absolute values of the cumulative sum of each observation will be calculated.

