### Treatment reproducibility

Intra-fraction and inter-fraction R_BH_ is measured for each participant. For all treatment fractions, 3D volumetric Cone Beam Computed Tomography (CBCT) images are acquired using Elekta XVI™ (Elekta, Stockholm, Sweden) before treatment delivery. For participants treated with SABR, post-correction, during, and post-treatment CBCTs are also acquired. Each CBCT is a 360° acquisition using several BHs, with acquisition paused between BHs. The CBCT is automatically fused to the planning CT with a bone algorithm to correct patient setup. Then, a soft-tissue fusion corrects for tumor position. Tumor displacement is measured as the correction applied after accounting for patient setup. Treatment R_BH_ of tumour is defined as follows:*Inter-Fraction R*_*BH*_ Position, in three planes, of the tumor/surrogate on planning CT compared to the position on CBCT1, at each treatment fraction. Results will be collated for all fractions, and averaged.*Intra-Fraction R*_*BH*_ For those participants with multiple CBCTs per fraction, the position, in three planes, of the tumor/surrogate on CBCT1 compared to the position on each subsequent CBCT, at each treatment fraction. The mean values of the absolute value of the cumulative sum of each observation will be calculated.

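### R_BH is written as the absolute value of a cumulative sum of displacements already measured from a fixed reference, so applied literally it is not a mean absolute displacement

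*Protocol article*

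**What the plan says.** Under Pre-planning reproducibility and stability, the protocol article sets out the R_BH observations: "Cranio-caudal position of the tumor/surrogate at the beginning of BH1 is compared to the position at beginning of BH2-5. Four observations are recorded per technique". It then gives the summary: "The absolute value (ignoring direction) of the cumulative sum of each observation is determined, and then averaged". In the same paragraph S_BH is summarised without any cumulative sum: "The mean of the absolute value (ignoring direction) of each observation is then calculated".

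Planning reproducibility compares CT2-4 with CT1, which gives three observations, and states: "The mean of the absolute values of the cumulative sum of each observation will be calculated". Treatment reproducibility compares each later CBCT with CBCT1 for intra-fraction R_BH and states: "The mean values of the absolute value of the cumulative sum of each observation will be calculated". Inter-fraction R_BH has a different rule, with neither a cumulative sum nor an absolute value: "Results will be collated for all fractions, and averaged".

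Under Determination of treatment technique, R_BH has priority, with this tie rule: "If two or more techniques have equal (to nearest mm) mean R_BH_, then the technique with better S_BH_ is selected". The limit is: "A technique with mean R_BH_ and/or S_BH_ > 5 mm will proceed to free-breathing". Statistical analysis then compares R_BH between pre-planning, planning and treatment against ±2 mm.

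**The concern.** Every observation in these three definitions is already a displacement from one fixed position (BH1, CT1 or CBCT1). Nothing remains to accumulate. Summing signed displacements before taking the absolute value gives one of two other quantities, depending on how the phrase is read. Running sums count an early offset again in every later term. A single total lets opposite shifts cancel.

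R_BH enters primary outcomes a and c and the intra-fraction part of d. It also selects each participant's technique, which is outcome b. A definition that departs from mean absolute displacement can therefore change which technique is selected, how R_BH stands against 5 mm, and what the ±2 mm comparisons are comparing.

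**Working it through.** The article reports no computed R_BH, so it has no figure of its own to reproduce. The check applies the written rule.

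**Inputs from the article.** Four observations at pre-planning and three at planning, each against a fixed reference; a 5 mm limit; a ±2 mm margin; lowest R_BH selects the technique.

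**Inputs assumed.** Hold positions x_1 to x_5 are independent and normal with SD s = 1, 2 or 3 mm, in one axis. The article gives no within-patient SD, so a range is shown.

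**Formulas**, with d_i the displacement of hold i from the reference:
- Mean absolute: the average of |d_i|.
- Running sum: the average of |d_1|, |d_1 + d_2|, and so on.
- Total: |sum of d_i| / n.

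**Worked examples**
- Constant shift d, running sum: (1 + 2 + 3 + 4)d/4 = 2.5d with four observations, and (1 + 2 + 3)d/3 = 2.0d with three. A constant 2.5 mm therefore scores 6.25 mm at pre-planning. Mean absolute and total both give 2.5 mm.
- Alternating +d, -d, +d, -d: the running sums are d, 0, d, 0, which average 0.5d; the total is 0. With d = 6 mm, mean absolute is 6.0 mm, running sum 3.0 mm and total 0 mm.

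**Expected values.** The k-th running sum has variance (k + k²)s², so its SD is 1.414s, 2.449s, 3.464s and 4.472s for k = 1 to 4. The mean absolute value of a centred normal variable is 0.798 times its SD.
- Mean absolute: 0.798 × 1.414s = 1.13s, whatever the number of observations.
- Running sum, four observations: 0.798 × (1.414 + 2.449 + 3.464 + 4.472)s/4 = 2.35s.
- Running sum, three observations: 0.798 × (1.414 + 2.449 + 3.464)s/3 = 1.95s.
- Total, four observations: 0.798 × 4.472s/4 = 0.89s.

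Under running sums, pre-planning therefore exceeds planning by about 0.40s with identical motion: 0.40, 0.81 and 1.22 mm at s = 1, 2 and 3 mm. The last is 1.22/2 = 61% of the ±2 mm margin. Under mean absolute the difference is 0.

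**Share of techniques above 5 mm** (simulation, 200,000 draws)

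| s (mm) | Mean absolute | Running sum | Total |
|---|---|---|---|
| 1 | 0% | 7.8% | 0% |
| 2 | 2.6% | 38.4% | 2.6% |
| 3 | 15.0% | 56.9% | 13.6% |

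**Technique with lowest R_BH** (simulation, three techniques of equal s). Without the nearest-mm tie rule, the choice differs from the mean-absolute choice in 28% of participants (running sum) and 30% (total). With rounding to the nearest mm and ties settled by an independent random draw standing in for S_BH, the figures are 29-35% and 28-29%.

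**The case against.** The strongest defence is that the phrase is loose wording for something sound. Two benign readings exist.

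- The observations are successive differences. The pre-planning paragraph does begin by speaking of consecutive breath-holds, and a cumulative sum of successive differences returns exactly the displacement from BH1. For positions 0, 3, -1, 2, 4 it gives 3, -1, 2, 4. But the definition itself compares BH2-5 with BH1, and the planning and intra-fraction definitions also name a fixed reference.
- Absolute values are taken first, then summed and averaged, which is the mean absolute displacement. But the written order puts the sum inside the absolute value.

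Neither reading removes the fault in the text, though both make it plausible that staff compute the right quantity.

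Several stronger statements are tempting, and the article does not support them:
- That wrong values are in use. No computed R_BH is shown.
- That all the harms occur together. Cancellation to 0 mm arises only with the total. Inflation past 5 mm and the false gap between pre-planning and planning of up to 1.22 mm arise only with running sums.
- That no reading yields a displacement in mm. The total divided by n is the absolute mean offset from the reference, in mm; its defect is that it hides alternating shifts.
- That shifts cancel across the three planes. The text speaks of summing observations, not axes.
- That all of outcome d is affected. Inter-fraction R_BH uses no cumulative sum.

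The selection effect can also be put in proportion. With equal SDs no technique is truly better. With SDs of 1, 2 and 3 mm and no tie rule, the choice differs in 22% (running) and 28% (total), and the mean absolute displacement of the chosen technique worsens by only 0.14 and 0.24 mm on average. Even so, the steadiest technique is picked in 65% and 59% of participants instead of 81%.

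**Conclusion.** The point stands as a fault in the written definition. Followed literally, the rule does not give mean absolute displacement at pre-planning, planning or intra-fraction, and the article does not say which sum is meant. Outcomes a, b, c and the intra-fraction part of d are affected.

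The size depends on the reading. Running sums distort both the 5 mm comparison and the comparison of pre-planning with planning. The total leaves the 5 mm rate almost unchanged on average but can score large opposite shifts as 0. Either reading changes the technique with the lowest R_BH in a substantial minority of participants.

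The percentages rest on independent normal holds and the assumed SDs. The worked examples rest on neither. No view is taken on the 5 mm rule as a clinical rule; it serves here only as a threshold on R_BH.

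**What to change.** In Pre-planning reproducibility and stability, Planning reproducibility, and Treatment reproducibility (intra-fraction), define R_BH as S_BH already is: the mean of the absolute value of each displacement from the stated reference. For three-plane data, report it per axis, and use the cranio-caudal value for comparison with pre-planning.

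Give inter-fraction R_BH the same absolute-value definition. It now states only an average, in which opposite shifts can cancel if signed values are used, yet treatment R_BH is compared with the other stages at ±2 mm.

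State which formula has been used so far. Recompute any R_BH derived by cumulative sum, and report any participant whose technique selection would have differed.

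The cost is a wording change and a recalculation from displacements already recorded, with no new data. Recalculation corrects the reported R_BH but cannot change techniques already used, which is why differing selections need to be reported.

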**Fig. 3 Fig3:**
[figure not shown]
AP kV fluoroscopy image with fiducial markers (**a**—blue) and diaphragm position (**b**—red)

### Patient experience questionnaire

Participants are invited to complete a questionnaire (Additional file 1: Appendix 1) to evaluate their experience of each technique. The questionnaire, developed specifically for this study, as there was no available validated questionnaire, includes both quantitative questions using a Likert-type scale; and qualitative open-ended questions, allowing the participant to elaborate on their experience. Participants are asked to rank the techniques in order of their preference. As required, a staff member involved in the breathing and/or reproducibility and stability assessment will conduct a semi-structured interview with the patient to elicit responses to all applicable questions.

### Determination of treatment technique

Following the ABC-BH and pre-planning R_BH_ and S_BH_ assessments, selection of treatment technique is made according to the decision matrix (Fig. 4), with R_BH_ prioritized. If two or more techniques have equal (to nearest mm) mean R_BH_, then the technique with better S_BH_ is selected. A technique with mean R_BH_ and/or S_BH_ > 5 mm will proceed to free-breathing.

**Fig. 4 Fig4:**
[figure not shown]
Decision matrix for selection of treatment technique

### Planning reproducibility

Participants have all subsequent planning and treatment using the chosen BH technique. Four planning computed tomography (CT) scans are acquired for each participant. The scans are acquired sequentially within a 5 min timeframe, with no patient-repositioning between scans, to minimize the impact of repositioning or physiological variation. The Gross Tumor Volume (GTV), tumor surrogates and OARs are contoured on the first planning CT. Post-processing and measurements are completed using a customized workflow in MIM Maestro® software (MIM Software Inc, Cleveland OH). The first planning CT is automatically fused to subsequent CTs. Initially, a bone algorithm fusion corrects any gross patient misalignment. Then, a tumor, surrogate or fiducial marker fusion corrects for tumor/organ position. Contours are automatically generated onto each subsequent CT. Resultant contours are reviewed, and manually edited if required to account for deformation. The inter-BH displacement of the tumor and OARs are measured, with bone fusion as the starting position. Planning R_BH_ of tumour/surrogate and OARs is defined as follows:*R*_*BH*_ Position, in three planes, of the tumor/surrogate or OAR contour centroid and contour surface in CT1 compared to the position in CT2-4, resulting in three observations. The mean of the absolute values of the cumulative sum of each observation will be calculated.

### Treatment reproducibility

Intra-fraction and inter-fraction R_BH_ is measured for each participant. For all treatment fractions, 3D volumetric Cone Beam Computed Tomography (CBCT) images are acquired using Elekta XVI™ (Elekta, Stockholm, Sweden) before treatment delivery. For participants treated with SABR, post-correction, during, and post-treatment CBCTs are also acquired. Each CBCT is a 360° acquisition using several BHs, with acquisition paused between BHs. The CBCT is automatically fused to the planning CT with a bone algorithm to correct patient setup. Then, a soft-tissue fusion corrects for tumor position. Tumor displacement is measured as the correction applied after accounting for patient setup. Treatment R_BH_ of tumour is defined as follows:*Inter-Fraction R*_*BH*_ Position, in three planes, of the tumor/surrogate on planning CT compared to the position on CBCT1, at each treatment fraction. Results will be collated for all fractions, and averaged.*Intra-Fraction R*_*BH*_ For those participants with multiple CBCTs per fraction, the position, in three planes, of the tumor/surrogate on CBCT1 compared to the position on each subsequent CBCT, at each treatment fraction. The mean values of the absolute value of the cumulative sum of each observation will be calculated.

### Treatment efficiency

Total treatment time, T_BH_, and number of BHs required to deliver treatment are recorded for the first three fractions for all participants. From this, an estimate of treatment efficiency is determined, as the proportion of total treatment time in which delivery occurred.

## Statistical analysis

Sample size calculation indicates required recruitment of 14–27 participants to be powered to detect a 2 mm variation in reproducibility, assuming standard deviation of 2 mm or 3 mm respectively.

The R_BH_ and S_BH_ measurements during pre-planning will be collated and described for each participant and each BH method. The number of patients screened into each BH technique will be reported, along with descriptive statistics such as the mean and standard deviation (SD) for R_BH_ and S_BH_ in order to compare each technique. Paired *t* tests will be used to test for differences between the BURDIE-screened R_BH_ and S_BH_ with our institutional standard technique EBH, including subset analysis of those participants who do not screen into EBH. Further comparisons will be made to compare each BH technique’s mean R_BH_ and S_BH_ with the selected technique mean. Mixed effects models will be used to evaluate the multiple observations for each patient, and each technique.

The planning mean R_BH_ measurements will be compared with the pre-planning results for each participant, and allow an assessment of the correlation between the mean R_BH_ values at the two time-points. Paired *t* tests will be conducted to provide an estimate of the 95% confidence interval in the paired observations with a margin of ± 2 mm considered to reflect similarity and/or an indication of the non-inferiority margin. Bland–Altman plots, with Pitman’s test will be prepared to test for any indication of bias in the pre-planning and planning R_BH_ means. Tests for variation across each BH technique will be conducted, with assessments of the average R_BH_ values for each technique, the study population and comparisons to the pre-planning time-point.

To evaluate treatment R_BH_, correlation coefficients will be estimated as fixed-effects, to indicate the consistency between the inter-fraction and intra-fraction observations. The treatment mean R_BH_, will be compared to the pre-planning and planning results, and allow an assessment of the correlation between these paired means. The 95% confidence interval in the paired observations will be compared to a non-inferiority margin of ± 2 mm, with Bland–Altman plots and the Pitman’s test used to test for any indication of bias in the treatment R_BH_ for comparison with pre-planning and planning means. However, it is expected that that the difference between the pre-planning, planning and treatment values may reduce over time, and these differences will be assessed descriptively, and compared to the non-inferiority margin of ± 2 mm.

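### The paired test of screened R_BH against EBH reuses the breath-holds that chose the technique, so it tends to show an improvement even when the three techniques are equally reproducible

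*Protocol article*

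**What the plan says.** All places are in the protocol article.

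- **Selection.** The abstract says that pre-planning reproducibility and stability are "used to select the technique with which to proceed to planning and treatment". Under Determination of treatment technique, R_BH has priority and "If two or more techniques have equal (to nearest mm) mean R_BH_, then the technique with better S_BH_ is selected". Means above 5 mm lead to free-breathing.
- **Data.** Under Pre-planning reproducibility and stability, five breath-holds per technique give four R_BH observations against the first breath-hold and five S_BH observations. S_BH is defined at no other time point.
- **Test.** The paragraph of Statistical analysis that states that "measurements during pre-planning will be collated and described for each participant and each BH method" goes on to name paired t tests, "used to test for differences between the BURDIE-screened R_BH_ and S_BH_ with our institutional standard technique EBH, including subset analysis of those participants". That subset is everyone for whom another technique was chosen. The paragraph adds a comparison of each technique's mean "R_BH_ and S_BH_ with the selected technique mean".
- **After selection.** Under Planning reproducibility, all later planning and treatment use the chosen technique only.

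**The concern.** The screened R_BH is, to within rounding, the smallest of three noisy measurements, and one of the three is the comparator. A paired t test assumes that the mean difference is zero if screening does nothing. Here it is below zero even if screening does nothing, because the selection rule picks whichever technique happened to look best on those five breath-holds.

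The not-EBH subset consists of participants whose EBH did not win on those same data, so it shares the fault. So does the comparison of each technique with the selected-technique mean.

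This is the only planned test of individual screening against the institutional standard. The Discussion puts forward better reproducibility as the possible benefit of screening. As written, the p-value cannot separate a useful screen from picking the luckiest of three measurements.

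**Working it through.** **1. Which data can enter the test.** S_BH exists only at pre-planning. Participants not assigned EBH have no later EBH data. For them, the selected-versus-EBH contrast can only use the breath-holds that made the selection.

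**2. Sign of the difference.** For participant i let d_i = R_BH(selected) − R_BH(EBH).
- If EBH is selected, d_i = 0.
- Otherwise round(R selected) ≤ round(R EBH). So d_i can exceed 0 only when both round to the same millimetre, and then d_i < 1 mm.
- In simulation about 9% to 14% of differences were such reversals (mean R_BH 1.5 to 2.5 mm).

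**3. The plan's own figures.** The article gives 14 to 27 participants for 2 mm at SD 2 or 3 mm, without alpha or power. A paired t calculation with assumed two-sided alpha 0.05/3 and 80% power returns exactly 14 and 27. The sample size is not in dispute; both values of n are used below.

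A rough calculation with those SDs reads them as the SD of the paired difference and treats all of it as noise:
- The SD of one measurement is SD/√2, and the expected minimum of three normal values is −0.846 SD.
- SD 2: 0.846 × 1.414 = 1.2 mm. SD 3: 0.846 × 2.121 = 1.8 mm.
- One third select EBH and contribute zero, so the subset figures are 1.2/(2/3) = 1.8 mm and 1.8/(2/3) = 2.7 mm.

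This ignores rounding and any true difference between techniques, so it is on the high side. The target effect is 2 mm.

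**4. Simulation under the null.** Each participant has the same true reproducibility in all three techniques. Assumptions that are not in the article:
- normal breath-hold positions, so that mean R_BH = 2σ/√π
- between-participant CV 40%
- mean S_BH 0.8 mm
- all three techniques feasible for everyone
- no 5 mm free-breathing rule

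R_BH is read as the mean of |BH2–5 minus BH1|. Selection is by R_BH rounded to 1 mm, then by S_BH. The test is two-sided at 0.05, and the table counts rejections favouring screening (nominal 2.5%). The 1.5 mm row is in line with the 1.3 to 1.6 mm that the Background quotes for ABC.

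| Mean R_BH | Spurious R_BH gain | R_BH, n=14 | R_BH, n=27 | S_BH, n=14 | S_BH, n=27 |
|---|---|---|---|---|---|
| 0.7 mm | about 0.2 mm | 35–37% | 71% | about 34% | about 60% |
| 1.5 mm | 0.45 mm | 52–54% | 92–94% | 24–26% | 43–44% |
| 2.5 mm | about 0.9 mm | 73–76% | 99% | about 14% | 22–23% |

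Ranges within a cell come from repeat runs. The S_BH bias is about 0.1 mm at mean R_BH 1.5 mm. It falls as R_BH rises, because ties become rarer.

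In the not-EBH subset at 1.5 mm, the spurious gain is 0.67–0.68 mm (check: 0.45/(2/3) = 0.68), with false rates of 56–58% and 93%.

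A second model with other assumed noise (mean R_BH 0.6 to 3.5 mm) gave R_BH false rates of 38% to 87% at n=14 and 72% to nearly 100% at n=27.

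**5. Held-out version under the same null.** For each of the 10 ways to hold out two of five breath-holds, select on three, measure on two, then average per participant.
- Mean difference: within ±0.01 mm.
- Two-sided rejection: 4.5% to 5.6%, of which 1.1% to 1.8% favours screening. It is conservative in that direction.
- Power for an assumed true gain of 0.42 mm: about 10% at n=14 and 26% at n=27.

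**The case against.** **Choosing the best technique is the intervention, so a gain is expected.** That supports describing the gain. It does not support testing it against a null that the selection rule already breaks.

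**This is a pilot, and neither the aims nor the primary outcomes state a screened-versus-EBH hypothesis.** This stands, and it is why a descriptive report plus an interval is enough. It does not validate a test that the plan commits to.

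**A fuller analysis plan may deal with it.** The selection data, the test data and the test are all fixed in the article, and together they conflict. This is not a missing detail.

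**Planning and treatment give independent data.** They do, but only for the chosen technique. They supply no EBH contrast for participants assigned something else.

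**The inputs are assumed, the decision matrix figure is not visible, and the 5 mm rule was not simulated.** All true. The rates are therefore illustrations over a range. The sign argument in step 2 of the working needs none of the noise assumptions, only the selection rule as the text gives it.

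A reader might also infer more than the article supports:

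- *That S_BH is biased by construction in the same way.* It is not. S_BH enters only as the tie-break.
- *That EBH is never measured after selection.* Participants who screen into EBH are planned and treated in EBH. It is unmeasured only for the others.
- *That regression to the mean undermines the planning and treatment comparisons.* A shift of about 0.45 mm is small against the ±2 mm margin. Planning R_BH is also a different measure (three planes on CT, against cranio-caudal fluoroscopy), so no clean shift can be derived. The plan anticipates change between time points, saying that "it is expected that that the difference between the pre-planning, planning and treatment values may reduce over time", and assesses it descriptively.

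**Conclusion.** The concern holds for R_BH: the planned paired test against EBH is circular, and no reading of the article removes this. Under identical techniques and the assumed inputs, it falsely favours screening in about 35% to 76% of trials at n=14 and 71% to 99% at n=27, with a spurious gain of about 0.2 to 0.9 mm. For S_BH the rates are about 14% to 34% and 22% to 60%, through the tie-break alone. The not-EBH subset and the comparison with the selected-technique mean share the fault.

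This does not show that screening is useless, or that the selection procedure is wrong. It shows that this test cannot tell. The article gives no noise levels, so the sizes are assumption-based; the direction of the R_BH bias is not. The test should be changed before analysis.

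**What to change.** 1. Report the as-planned screened-versus-EBH comparison, the not-EBH subset and the comparison with the selected-technique mean descriptively, without p-values. State that they are biased towards screening.
2. For inference, use the held-out version on the same five breath-holds. In each of the 10 splits, apply the decision rule to three breath-holds and take R_BH and S_BH of the selected technique and of EBH from the other two. Average over splits per participant. Report the mean difference with its 95% confidence interval and a paired test.
3. Keep the assigned technique's pre-planning R_BH as the reference for planning and treatment, and state that it is somewhat too low because it was selected as the best of three. Do not substitute the held-out average. About 42–43% of split selections differ from the assigned technique under the null, and 34–40% when techniques truly differ (assumed spread). The average would therefore mix in techniques that the participant was not treated with.

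**Cost:** a change of wording and a short script, with no new imaging or participants. Selecting on three breath-holds slightly understates the benefit of selecting on five. Power is low (about 10% and 26% for an assumed true gain of 0.42 mm), so a non-significant result must not be read as no benefit, and the interval should carry the interpretation.
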